## Recruitment {15}

Recruitment of participants started at 17 April 2019 and will be continued until the required number of participants will be enrolled. Infants with a unilateral inguinal hernia will be identified by the (fellow) paediatric surgeon at the outpatient clinic or neonatal intensive care unit (NICU) of the participating centres (Fig. 1). Currently (dd. August 24th 2021), 302 patients are included in this study. To enhance patient participation in this trial, one researcher coordinates the potential inclusions in all participating centres and strives to limit the number of eligible patients that were missed for inclusion. Over the past year, there has been some delay due to COVID-19; however, we expect to complete the recruitment of patients in 6 to 12 months.

## Assignment of interventions: allocation

### Sequence generation {16a}

Study participants will be randomly assigned (1:1) to the intervention (contralateral exploration) or control group (no contralateral exploration) using Castor Electronic Data Capture (Castor EDC), a web-based electronic case record form and randomisation program that is compatible with the GCP guidelines [30].

### Concealment mechanism {16b}

Treatment allocation will be concealed by using a web-based application with a computer-generated list with varying block sizes that will not be disclosed and is stratified by centre. Participants and care providers are aware of allocation.

### Implementation {16c}

After obtaining informed consent, participants will be randomly allocated to one of the two study groups by the researcher using Castor EDC.

## Assignment of interventions: blinding

### Who will be blinded {17a}

Blinding of patients, parents or caregivers is impossible because of the nature of the intervention since a scar will develop and instructions have to be given for the postoperative treatment of the wound(s). Outcome assessors and statistician blinded to study groups will conduct all analysis.

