## Outcomes {12}

### Primary outcome measure

Primary outcome is the proportion of reoperations within 1 year after primary hernia repair. This will be calculated using the number of infants that undergo a second operation related to inguinal hernia repair within 1 year following primary repair, as a fraction of the total number of infants in that group. All participants are seen by a (fellow) paediatric surgeon at the outpatient clinic or via a digital consult 1 year after primary hernia repair. The latter is done to score development of contralateral hernia, testicular atrophy and/or recurrence.

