#### Complications of anaesthesia and surgery

Complications related to inguinal hernia within 1 year after primary repair are as follows: wound infection, hematoma, hydrocele, testicular atrophy, apnoea or inguinal hernia recurrence. Apnoea, wound infection, hematoma and hydrocele will be assessed during hospital admission via monitoring (if applicable) and by the (fellow) paediatric surgeon. After hospital discharge, these complications will be assessed through a phone call performed by one of the investigators 4 weeks following surgery. Testicular atrophy and inguinal hernia recurrence will be assessed at the outpatient clinic 1 year following surgery. If there is partial or complete testicular atrophy of one testis (i.e. one of the testes is smaller compared to the other at follow-up), additional ultrasonography of both testes will be performed. Complications are defined as:
Testicular atrophy: No palpable testicular tissue in scrotum (=complete testicular atrophy) or testis documented to be smaller at follow-up than at time of inguinal hernia repair (=partial testicular atrophy) at operated side(s).Wound infection/surgical site infection: Infection occurring within 30 days of surgery; infection involving only the skin and subcutaneous tissue; at least one of the following: (a) purulent discharge from a superficial infection or (b) organisms isolated from aseptically obtained wound culture; and at least one of the following signs of infection: (a) pain or tenderness, (b) localised swelling and (c) redness or hyperthermia [24].Apnoea: Apnoea of infancy is defined as “an unexplained episode of cessation of breathing for 20 seconds or longer, or a shorter respiratory pause associated with bradycardia, cyanosis, pallor, and/or marked hypotonia requiring intervention”. Types of interventions recorded will include stimulation, assisted ventilation, continuous positive airway pressure (CPAP), endo-tracheal intubation and administration of methylxanthine [25].Recurrence: the hernia returns at the previously operated side and a reoperation on the same side is warranted.

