### Procedure for unblinding if needed {17b}

This is an open label trial; therefore, an unblinding procedure does not apply.

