## Data collection and management

### Plans for assessment and collection of outcomes {18a}

Data of participants and findings for primary and secondary outcome measures will be recorded by the (fellow) paediatric surgeon or one of the investigators in a web-based electronic case record form using Castor EDC [30]. Parents/caretakers will use the online KLIK PROM (patient-reported outcome measures) portal (www.hetklikt.nu) to answer questionnaires.

The study will collect the following baseline characteristics and data from the participants: sex, gestational age, birth weight, comorbidities, inguinal hernia in first degree siblings, age and weight at day of surgery, preoperative size of both testes (in boys), side of the inguinal hernia and other hernia characteristics (e.g. preoperative history of hernia incarceration and surgical findings during contralateral exploration (i.e. presence of a PPV or not), total duration of surgery and hospital admission, total number of hospital visits and complications.

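### The protocol calls outcome assessors blinded, but its own assessment arrangements are unblinded; some detection bias in the reoperation endpoint is plausible, of unknown size

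*Protocol article*

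**What the plan says.** The blinding item {17a} reads: "Outcome assessors and statistician blinded to study groups will conduct all analysis". The same item says that blinding of patients, parents or caregivers is "impossible because of the nature of the intervention since a scar will develop".

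Elsewhere in the protocol article:

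- Concealment mechanism {16b}: "Participants and care providers are aware of allocation".
- Procedure for unblinding {17b}: "This is an open label trial; therefore, an unblinding procedure does not apply".
- Primary outcome measure: "All participants are seen by a (fellow) paediatric surgeon at the outpatient clinic or via a digital consult 1 year after primary hernia repair". The stated purpose of that contact is to score contralateral hernia, testicular atrophy and recurrence.
- Complications of anaesthesia and surgery: in hospital, the surgeon assesses complications, with monitoring where applicable. After discharge, "these complications will be assessed through a phone call performed by one of the investigators 4 weeks following surgery".
- Plans for assessment and collection of outcomes {18a}: "findings for primary and secondary outcome measures will be recorded by the (fellow) paediatric surgeon or one of the investigators".
- Health-related quality of life: parents or caretakers complete the questionnaires.

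The primary outcome is the proportion of infants who undergo a second operation related to inguinal hernia within 1 year. The article describes no separate masked assessor and no masked review of the reason for reoperation.

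**The concern.** A reader who judges risk of bias goes to the blinding item first, and there finds outcome assessors named as blinded. If no assessor is in fact blinded, the protocol credits the trial with a protection that it does not have.

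This matters more for the primary endpoint than for a hard event such as death. A second operation is a recorded fact, but it follows a clinical judgement that a swelling is a hernia. That judgement can be made knowing that the opposite groin was never opened (control arm), or that it was explored and either found closed or repaired (intervention arm). The plausible direction is somewhat more contralateral reoperations in the control arm, which would favour exploration. With few expected events, a small number of such operations could matter.

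**Working it through.** **Step 1. The passages side by side.**

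| Outcome | Who assesses or reports it | Can that person know the allocation? |
|---|---|---|
| Contralateral hernia, recurrence, testicular atrophy at 1 year | (Fellow) paediatric surgeon, in clinic or by digital consult | Yes: care providers are aware {16b}, and scars show it on examination {17a} |
| In-hospital complications | (Fellow) paediatric surgeon, plus monitoring | Yes, as a care provider |
| Complications at 4 weeks | An investigator, by telephone | Likely (parents know, and a researcher performs the randomisation {16c}), but not stated |
| Quality of life, distress, anxiety | Parents or caretakers | Yes |
| Recording of all primary and secondary findings | Surgeon or investigator {18a} | Yes for the surgeon; not stated for the investigator |

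No row describes a masked assessor. The only person in item {17a} whose blinding fits the rest of the document is the statistician.

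**Step 2. Reproduce the plan's sample size, to fix the expected event counts.** Inputs from Sample size {14}: 10% v 2.5%, power 0.80, two-sided alpha 0.05. Allocation is 1:1 {16a}.

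- Mean rate = (0.10 + 0.025)/2 = 0.0625; difference d = 0.075.
- n = [1.960·√(2·0.0625·0.9375) + 0.842·√(0.10·0.90 + 0.025·0.975)]² / 0.075² = (0.6709 + 0.2846)² / 0.005625 = 162.3, that is 163 per arm.
- With continuity correction: (162.3/4)·[1 + √(1 + 4/(162.3·0.075))]² = 188.06, that is 189 per arm and 378 in total. This matches the stated 378.

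**Step 3. Expected events.** 189 × 0.10 = 18.9 ≈ 19 in the control arm; 189 × 0.025 = 4.7 ≈ 5 in the intervention arm.

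**Step 4. Illustration.** Suppose k of the 19 control reoperations occurred only because the allocation was known. The documents give no value for k; every k above 0 is an assumption. Three tests are shown because the planned primary estimate is an adjusted odds ratio from logistic regression, which cannot be computed without data. The crude logistic (Wald) version uses SE(log OR) = √(1/a + 1/(189−a) + 1/5 + 1/184), with a the control events and the OR taken as control v intervention.

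| k | Events | Difference (points) | Fisher exact p | Uncorrected two-proportion p | Crude OR, Wald p |
|---|---|---|---|---|---|
| 0 | 19 v 5 | 7.4 | 0.005 | 0.003 | 4.11, 0.006 |
| 3 | 16 v 5 | 5.8 | 0.023 | 0.014 | 3.40, 0.019 |
| 5 | 14 v 5 | 4.8 | 0.057 | 0.034 | 2.94, 0.042 |
| 6 | 13 v 5 | 4.2 | 0.088 | 0.053 | 2.72, 0.062 |

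Worked for 14 v 5: OR = (14/175)/(5/184) = 2.944; log OR = 1.080; SE = √(0.0714 + 0.0057 + 0.2000 + 0.0054) = 0.532; z = 2.03; p = 0.042.

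**Step 5. The same question with no true effect.** Let both arms have the same true rate p₀, and let the control arm gain an excess e. The chance of a significant result in favour of exploration is Φ{[e·√189 − 1.960·√(2·p̄·(1−p̄))] / √(p₁(1−p₁) + p₀(1−p₀))}, with p₁ = p₀ + e and p̄ = (p₁ + p₀)/2. Without bias this chance is 2.5%.

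| p₀ | e = 1 point | e = 2 points | e = 3 points |
|---|---|---|---|
| 2.5% | 8% | 18% | 32% |
| 5% | 6% | 13% | 22% |
| 10% | 5% | 9% | 15% |

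Both tables show how sensitive the result is to a few events. Neither estimates how much bias there will be.

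**The case against.** **The sentence is about analysis.** It says that blinded people will conduct the analysis, and the neighbouring items openly say that care providers know the allocation and that the trial is open label. This stands in part: a careful reader will not be wholly misled. But outcome assessors do not conduct the analysis, and the item is the one that names who is blinded. On the analysis-only reading the term is still wrong and needs correction.

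**The endpoint is the surgeon's own decision.** A reader might infer that the assessing surgeons decide on reoperation themselves. The documents do not support this: no section says who decides, or that it is the original surgeon. The background section says that a contralateral hernia almost invariably leads to a second operation, which limits discretion after diagnosis. What remains is judgement in making the diagnosis.

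**The bias would fall in the control arm only.** A reader might infer this too. The endpoint covers any second operation related to inguinal hernia, so it includes ipsilateral recurrence, which can occur in both arms. Moreover, knowing that a groin was found closed or repaired is information that exploration itself produces. Part of any difference in threshold is therefore a real effect of the strategy.

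**No clinical outcome is free of this problem.** That is also too strong. Anaesthesia time, days in hospital, monitored apnoea and testicular ultrasonography leave little room for judgement, and it is not stated that the 4-week caller knows the allocation.

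**The scenarios are invented.** Correct: 5 of 19 is 26% of control reoperations, and nothing in the protocol supports that share. Loss of significance at 14 v 5 also appears only with Fisher's test, which is not the planned analysis.

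**Conclusion.** The contradiction holds and is certain from the text: item {17a} names outcome assessors as blinded, while the sections on outcomes, data collection, concealment and unblinding describe assessment by people who know the allocation or can see it. The protocol should not claim this safeguard.

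The consequence for the primary endpoint is weaker. Some detection bias towards more contralateral reoperations in the control arm is plausible, because the diagnosis that precedes surgery can be made with the allocation known. Its size is unknown and may be small. The 16 v 5 and 14 v 5 scenarios rest on assumed shares of allocation-driven operations and on the planned rates of 10% and 2.5%. They show only that about five or six events separate a clear result from a borderline one. They are no reason to expect a false conclusion. The point is worth acting on because the correction is cheap.

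**What to change.** 1. In item {17a}, state that clinical and parent-reported outcomes are assessed unblinded, and that only the statistician (the analysis) is blinded to group.
2. For every second operation, take from the operation report the side, the indication and the operative finding. Surgical findings at exploration, including whether a patent processus vaginalis (PPV) is present, are already collected {18a}.
3. Pre-specify, in the protocol or the statistical analysis plan, a sensitivity analysis of the primary endpoint that counts only reoperations with a true hernia documented, reported separately for the contralateral and ipsilateral sides. The primary analysis is unchanged.

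A PPV alone should not count as confirmation. The protocol says that not every PPV becomes a hernia and that a PPV found at exploration is repaired. Incidental PPVs therefore remain in unexplored control groins but are closed in the intervention arm. A criterion that accepts them would act differently by arm and could retain the very excess that it is meant to test. Masking the 4-week telephone caller would not help here, because that call does not determine the primary endpoint.

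Cost: the claim of blinded assessors is given up, a few fields are added to the case report form, and one small analysis is added. No extra staff are needed. If operation reports are on file, the fields can also be completed for children already enrolled (302 at 24 August 2021). One limit remains: the operative finding is itself recorded by a surgeon who knows the allocation, so the analysis reduces the concern but does not remove it.

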### Procedure for unblinding if needed {17b}

This is an open label trial; therefore, an unblinding procedure does not apply.

## Data collection and management

### Plans for assessment and collection of outcomes {18a}

Data of participants and findings for primary and secondary outcome measures will be recorded by the (fellow) paediatric surgeon or one of the investigators in a web-based electronic case record form using Castor EDC [30]. Parents/caretakers will use the online KLIK PROM (patient-reported outcome measures) portal (www.hetklikt.nu) to answer questionnaires.

The study will collect the following baseline characteristics and data from the participants: sex, gestational age, birth weight, comorbidities, inguinal hernia in first degree siblings, age and weight at day of surgery, preoperative size of both testes (in boys), side of the inguinal hernia and other hernia characteristics (e.g. preoperative history of hernia incarceration and surgical findings during contralateral exploration (i.e. presence of a PPV or not), total duration of surgery and hospital admission, total number of hospital visits and complications.

#### Health-related quality of life (HRQOL) and parental distress and anxiety

HRQOL of the operated infant will be assessed using the TAPQOL (TNO-AZL Preschool Children Quality of Life), a validated parent-reported questionnaire that is clustered into 12 multi-item scales in which questions are answered on a 3-point Likert scale, with higher scores (range 0–100) indicating better HRQOL [26]. Parental distress and anxiety levels will be measured with the State-Trait Anxiety Inventory (STAI) [27], a validated questionnaire that measures State Anxiety on a 4-point scale indicating greater anxiety when revealing higher scores. Last, parental distress will be measured using a brief version of the Distress Thermometer for Parents (DT-P), including the thermometer on which parents rate their distress (from 0, no distress, to 10, extreme distress) and a problem list to identify sources of distress in two domains: emotional and parenting [28]. The DT-P is a well-validated, brief screening instrument that is frequently used in Dutch clinical practice as quick screening to identify distress and everyday problems in parents of children who need medical treatment.

### Plans to promote participant retention and complete follow-up {18b}

Once a patient is enrolled and randomised, the researchers will make every reasonable effort to follow the study participant for the entire study period. Questionnaires (and if necessary reminders for completion) are sent using an online portal, thereby enabling parents to complete them at any convenient moment. Patients withdrawn from treatment will be asked to visit the outpatient clinic 1 year after surgery to investigate the primary endpoint of the study.

### Data management {19}

The trial will be conducted according to the study protocol and in compliance with the GCP guideline, to provide assurance that the rights, safety and well-being of trial subjects are protected and that the trial data are credible. Data are collected by trained local research staff using digital case report forms (CRFs), stored safely and encoded according to the central Information Technology (IT)-regime and standard operating procedures for FAIR (Findable, Accessible, Interoperable and Reusable) research data management. Questionnaires will be answered online and output will be stored in SPSS (Statistical Package for the Social Sciences). Raw data including metadata are available through a repository and under conditions available upon request.

### Confidentiality {27}

To ensure the privacy of participants, all the participants’ data will be encoded and only accessible to the principal investigator, coordinating investigator and project leader. Collected data from all centres will be stored at the Amsterdam UMC for 15 years.

### Plans for collection, laboratory evaluation, and storage of biological specimens for genetic or molecular analysis in this trial/future use {33}

Not applicable; these specimens are not collected.

## Statistical methods

### Statistical methods for primary and secondary outcomes {20a}

Data will be assessed using IBM SPSS Statistics Version 25. All statistical testing will be performed two-sided with *α* = .05 and according to the intention-to-treat-principle.

#### Primary study parameter

Primary outcome is the proportion of reoperations within 1 year after primary hernia repair. The number and percentage of reoperations by 1 year after primary hernia repair will be reported for each treatment group. Besides a crude analysis, a logistic regression analysis will be performed adjusted for centre and possible confounders (sex, gestational age at birth and initial hernia side). The primary-effect estimate will be the adjusted odds ratio, reported with the corresponding 95% confidence interval (CI).

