## Sample size {14}

Data from the latest systematic review shows that the incidence of infants younger than 6 months of age who develop MCIH is 12.4% [4]. Retrospective data from the Emma Children’s Hospital AMC, where in 2000/2001 contralateral exploration was routinely performed, shows similar results: 8/92 patients did not undergo contralateral exploration and subsequently one patient (12.5%) developed MCIH. Eighty-four patients underwent unilateral hernia repair with contralateral exploration of which one patient (1.2%) developed MCIH.

The expected percentage of children requiring one or more reoperations because of MCIH in the first year following hernia repair is approximately 10%. We consider a reduction of children requiring reoperation from 10 to 2.5% as clinically relevant. A total sample size of 378 patients is needed to detect such a reduction with a power of 0.80 at a two-sided alpha of 0.05 (nQuery Advisor 7.0) [29]. Taking into account 10% loss to follow-up, we need to include 416 children.

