#### Secondary study parameters

Secondary outcomes include the length of hospital stay and duration of operations (including anaesthesia time), complications of surgery and the health-related quality of life (HRQOL) of the operated infants and parental distress and anxiety. Mean (standard deviation, SD) or median (interquartile range, IQR) differences and corresponding 95% CIs will be calculated for length of hospital stay and duration of operations (including anaesthesia time). Odds ratio together with the 95% CI will be calculated for complications. Linear and logistic regression analysis will be performed to adjust for centre and possible confounders (sex, gestational age at birth and initial hernia side). Differences in HRQOL and parental distress and anxiety at baseline before surgery, 4 weeks and 1 year after primary hernia repair and, if relevant, prior to and 4 weeks after re-operation for MCIH will be reported using median and interquartile ranges.

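### The adjusted odds ratio prescribed for complications will often be non-estimable at the protocol's own general rates; the primary odds ratio is modestly too extreme but validly tested

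*Protocol article*

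**What the plan says.** Under Primary study parameter the article reports the number and percentage of reoperations per group and a crude analysis. It then says that "a logistic regression analysis will be performed adjusted for centre and possible confounders (sex, gestational age at birth and initial hernia side". It adds that "The primary-effect estimate will be the adjusted odds ratio", with a 95% confidence interval.

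Under Secondary study parameters it says: "Odds ratio together with the 95% CI will be calculated for complications". The next sentence there calls for linear and logistic regression with the same adjustment set. It names no alternative for outcomes with very few events.

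The planning figures are in Sample size {14}: "We consider a reduction of children requiring reoperation from 10 to 2.5% as clinically relevant", and "A total sample size of 378 patients is needed to detect such a reduction", "with a power of 0.80 at a two-sided alpha of 0.05". Allocation is 1:1.

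Background and rationale {6a} gives complication rates for children in general: wound infection 0.6–1.2%, haematoma 0.1%, testicular atrophy 0–0.3%, ipsilateral recurrence 0.4–1.2%. For preterm babies it gives recurrence 2–8.6% and testicular atrophy 2–30%. It puts apnoea at up to 12%.

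**The concern.** An odds ratio needs events in both arms. If one arm has none, the maximum-likelihood estimate is zero or infinite; if neither has any, it is undefined. Adding centre, sex, gestational age and hernia side does not cure this. Several listed complications are rare enough for it to be a likely result.

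The harm side of the comparison is at stake. The Objectives section hypothesises that exploration carries no more surgical complications than repair of a symptomatic hernia, and that its benefit may outweigh its burden. A table of infinite or blank odds ratios could neither support nor contradict that.

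The primary model has the same weakness in mild form: few events for the number of terms, which pulls a maximum-likelihood odds ratio away from 1.

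**Working it through.** **Planning figure.** With rates 0.10 and 0.025, mean 0.0625, power 0.80 and two-sided alpha 0.05, the usual two-proportion formula is

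n = [1.96√(2 × 0.0625 × 0.9375) + 0.8416√(0.10 × 0.90 + 0.025 × 0.975)]² / 0.075² = 162.3 per arm.

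The continuity correction, n/4 × [1 + √(1 + 4/(0.075n))]², gives 188.1, so 189 per arm and 378 in total. The stated figure is reproduced, and 189 per arm is used below.

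**Complications.** Assume the same rate p in both arms. Expected events per arm are 189p. The chance that one given arm is empty is q = (1 − p)^189, and the chance that at least one is empty is 1 − (1 − q)².

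| Complication | p | Events per arm | q | At least one arm empty |
|---|---|---|---|---|
| Haematoma | 0.1% | 0.2 | 0.828 | 97% |
| Testicular atrophy | 0–0.3% | 0–0.6 | 1–0.567 | 100–81% |
| Wound infection | 0.6–1.2% | 1.1–2.3 | 0.321–0.102 | 54–19% |
| Recurrence | 0.4–1.2% | 0.8–2.3 | 0.469–0.102 | 72–19% |
| Recurrence, preterm rates | 2–8.6% | 3.8–16.3 | 0.022 to below 0.001 | 4% to about 0 |
| Atrophy, preterm rates | 2–30% | 3.8–56.7 | 0.022 to about 0 | 4% to about 0 |
| Apnoea | 12% | 22.7 | about 0 | about 0 |

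The atrophy rows use all 189 infants; only boys are at risk, so real counts are lower.

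Simulation of the prescribed adjusted model agrees (1,500 trials per rate, 378 infants, seven unequal centres, no true difference). The treatment odds ratio was non-estimable in 20%, 54%, 79% and 97% of trials at 1.2%, 0.6%, 0.3% and 0.1%.

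An estimable odds ratio says little at these counts. With 2 events in each arm of 189, the standard error of the crude log odds ratio is √(1/2 + 1/2 + 1/187 + 1/187) = 1.005, so the 95% interval is exp(±1.96 × 1.005) = 0.14 to 7.2. The risk difference is 0 points, with a Newcombe score interval of −2.8 to 2.8. With 2 events against 0 there is no finite odds ratio, but the risk difference is 1.1 points (−1.1 to 3.8).

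**Primary outcome.** Expected reoperations are 189 × 0.10 + 189 × 0.025 = 18.9 + 4.7 = 23.6. If the seven named sites are fixed effects, the model has 1 + 6 + 3 = 10 terms besides the intercept, or 23.6/10 = 2.4 events per term. With five centres it has 1 + 4 + 3 = 8 terms, or 3.0 per term.

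The planned odds ratio is (0.025/0.975)/(0.10/0.90) = 0.231. Two independent sets of simulations of the adjusted model gave:

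- geometric-mean odds ratio 0.197–0.207, which is 1 − 0.207/0.231 = 10% to 1 − 0.197/0.231 = 15% too extreme;
- median 0.210–0.221, or 4–9% too extreme.

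One set (3,000 trials per scenario) also gave:

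- crude geometric mean 0.211–0.218;
- coverage 96.8–97.7%, type I error 4.3%, power 0.86–0.875;
- non-estimable treatment odds ratio in about 1% of trials;
- Firth-penalised geometric mean 0.235–0.238, close to the true 0.231.

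On the absolute scale the true difference is 7.5 points. Raw differences, and differences standardised from the ordinary logistic model, averaged 7.4–7.7. Those standardised from the Firth model averaged 8.2–8.5, because the penalty pulls predicted risks towards one half.

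**The case against.** The strongest case on the other side has four parts.

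*The general rates may not apply.* The trial enrols infants under 6 months, some from neonatal intensive care, and plans a subgroup born before 37 weeks. Apnoea is a listed complication and could give about 23 events per arm. Hydrocele has no stated rate. This stands: a reader might infer that every complication is too rare to model, and the protocol's figures do not support that.

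*Complications might be analysed as a composite.* The text does not say. Adding the four general rates without overlap gives 1.1% (0.6 + 0.1 + 0 + 0.4) to 2.8% (1.2 + 0.1 + 0.3 + 1.2), or 189 × 0.011 = 2.1 to 189 × 0.028 = 5.3 events per arm before apnoea and hydrocele. A composite would ease the problem, but would not give estimates for the separately defined complications.

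*The primary analysis is sound.* A reader might infer from 2.4 events per term that the headline result is unreliable. Coverage, type I error and power are all acceptable. In the scenarios without covariate effects, about two thirds to three quarters of the log-scale bias is already in the crude odds ratio, so it comes mainly from few events and less from the adjustment. A centre without events makes its own coefficient diverge but leaves the treatment odds ratio estimable. A reader might also infer that the absolute effect goes unreported; per-group percentages are promised, and the economic evaluation gives cost per reoperation prevented.

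*The rest is detail for the analysis plan.* How centre is coded is such detail, and adjusting for it suits randomisation stratified by centre. The effect measure and adjustment set, however, are fixed in the article itself.

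**Conclusion.** The point holds for rare complications. At the protocol's general rates, the prescribed odds ratio is very likely to be non-estimable for haematoma and testicular atrophy, and has a 19–54% and 19–72% chance of being so for wound infection and recurrence. It does not hold for apnoea near 12%, nor for recurrence or atrophy near the upper preterm rates. The true rates in this mixed population may lie in between.

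For the primary outcome the point is a refinement. The estimate is modestly too extreme and its test is valid; nothing in the documents supports calling the primary analysis invalid. A risk difference with an interval is still worth adding, because the planning effect is a fall from 10% to 2.5% and the article does not commit to such an interval.

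The complication figures assume equal rates in both arms, 189 evaluable infants per arm and separate analysis of each complication. The simulations assume centre sizes (equal or unequal) and covariate effects (none or modest) that the documents do not give.

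**What to change.** **Complications.** For rare complications, report counts, percentages and unadjusted risk differences with score or exact 95% intervals. Keep the adjusted logistic model only where events allow, for example apnoea, or recurrence and atrophy if they occur near the upper preterm rates. State the minimum event count in advance.

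**Primary outcome.** Report an adjusted risk difference with 95% interval beside the adjusted odds ratio. Choose one method beforehand: standardisation from the ordinary logistic model, which keeps all covariates, or a centre-stratified Mantel-Haenszel difference, which drops sex, gestational age and hernia side. Use Firth penalisation only for the odds ratio itself, since standardising from it overstates the risk difference (8.2–8.5 points against 7.5).

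The cost is revised analysis wording, a little extra analysis work and a routine outside base SPSS. No further data or participants are needed.
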